## Abstract

**Background:**

Creutzfeldt-Jakob Disease (CJD) is the most common prion disease in humans causing a rapidly progressive neurological decline and dementia and is invariably fatal. The familial forms (genetic CJD, gCJD) are caused by mutations in the *PRNP* gene encoding for the prion protein (PrP). In Israel, there is a large cluster of gCJD cases, carriers of an E200K mutation in the *PRNP* gene, and therefore the largest population of at-risk individuals in the world. The mutation is not necessarily sufficient for the formation and accumulation of the pathological prion protein (PrP^sc^), suggesting that other, genetic and non-genetic factors affect the age at symptoms onset. Here we present the protocol of a cross-sectional and longitudinal natural history study of gCJD patients and first-degree relatives of gCJD patients, aiming to identify biological markers of preclinical CJD and risk factors for phenoconversion.

**Methods:**

The study has two groups: Patients diagnosed with gCJD, and first-degree healthy relatives (HR) (both carriers and non-carriers of the E200K mutation in the *PRNP* gene) of patients diagnosed with gCJD. At baseline, and at the end of every year, healthy participants are invited for an “in-depth” visit, which includes a clinical evaluation, blood and urine collection, gait assessment, brain MRI, lumbar puncture (LP), and Polysomnography (PSG). At 6 months from baseline, and then halfway through each year, participants are invited for a “brief” visit, which includes a clinical evaluation, short cognitive assessment, and blood and urine collection. gCJD patients will be invited for one “in-depth” visit, similar to the baseline visit of healthy relatives.

**Discussion:**

This continuous follow-up of the participants and the frequent assessments will allow early identification and diagnosis in case of conversion into disease. The knowledge generated from this study is likely to advance the understanding of the underlying clinicopathological processes that occur at the very beginning of CJD, as well as potential genetic and environmental risk factors for the development of the disease, therefore advancing the development of safe and efficient interventions.

**Trial registration:**

The study is an observational study. It has registered retrospectively in https://clinicaltrials.gov/ and has been assigned an identification number NCT05746715.

**Supplementary Information:**

The online version contains supplementary material available at 10.1186/s12883-023-03193-8.

## Background

Creutzfeldt-Jakob Disease (CJD) is the most common prion disease in humans. It results from a conformational change of the normal prion protein (PrP^c^) into a pathological protein (PrP^sc^) that aggregates in the central nervous system [1]. Once formed, the initial PrP^sc^ oligomers can act as seeds for further misfolding of normal cellular PrP^c^ in a cascade that leads to neuronal death, as well as to the clinical manifestations of the disease.

Early symptoms are nonspecific and may include headaches, anxiety, and behavioral changes. Later, diffuse neurological impairment appears, including cognitive decline, cerebellar ataxia, pyramidal, and extrapyramidal deficits, disturbances of vision, and myoclonus. CJD can be etiologically classified into transmitted, sporadic (sCJD), and genetic forms (gCJD). The familial forms are caused by mutations in the PRNP gene that encodes for the prion protein (PrP). The largest cluster of gCJD cases exists in Jews of Libyan and Tunisian ancestry, carrying an E200K mutation (Glu to Lys substitution) in the *PRNP* gene. Approximately 200,000 Libyan Jews live in Israel, resulting in the largest population of at-risk individuals in the world [2].

The disease is invariably fatal, and survival is between several months to 1 year [3], with a mean survival from onset to death of 7.6 months [4]. Thus, by the time the disease is diagnosed, the neural pathology is extensive, and the neurodegeneration is vast. The presence of a genetic mutation may help identify individuals at risk for developing the disease as the penetrance of the mutation approaches 100% [5]. Carriers of the E200K mutation are born with this dominantly inherited mutation, but most remain asymptomatic until middle age, and some develop the disease as late as 80 years old [5].

E200K-PrP is initially formed as a normal PrP^c^ isoform [6]. Therefore, the mutation is not necessarily sufficient for the formation and accumulation of PrP^sc (6)^. This fact suggests that other, genetic and non-genetic factors affect the age at symptoms onset. The *CYP4 × 1* gene may influence the age at onset in patients with gCJD due to the E200K mutation and in sCJD [7]. Inheritance of gCJD with E200K mutation may exhibit anticipation (an earlier symptom onset or more severe presentation in offspring) [8]. However, this claim requires further investigation [9]. Other modifiers remain obscure.

Definitive diagnosis of CJD requires autopsy or brain biopsy. Clinical diagnostic criteria for CJD include a combination of cerebrospinal fluid (CSF) biomarkers, magnetic resonance imaging (MRI), electroencephalography (EEG), and clinical symptoms [10]. Early diagnosis of CJD remains challenging because the clinical manifestations of prion diseases at onset are variable and non-specific. Recently, testing of CSF with new in-vitro PrP^sc^ amplification technology, and designated real-time quaking-induced conversion (RT-QuIC), has shown considerable promise as a highly specific and sensitive tool for the diagnosis of sCJD [11]. RT-QuIC is a protein aggregation assay using quaking to induce misfolding of normal prions into PrP^sc^, with simultaneous fluorescent readout [12]. CSF RT-QuIC has proven to be a relatively sensitive (73-97%) [13, 14] and a highly specific biomarker (99-100%) [12, 15–17] for diagnosing CJD, and it is now part of the standard diagnostic criteria [10].

As with many neurodegenerative diseases, subtle clinical symptoms are likely to present even before diagnostic criteria are met. Based on the manifestation at the time of diagnosis, several clinical symptoms and signs seem to be common in most patients. These include visual deficits, balance and gait changes, sleep disturbances, as well as cognitive and behavioral impairments. Thus, it is possible that a more sensitive assessment could detect these changes before diagnosis.

Presently, diagnosis at the pre-clinical or prodromal stage is not feasible, as no validated blood biomarker for the prediction of symptoms onset exists. Previous attempts have been made to characterize the prodromal stage. Lee et al. tested a relatively large number of E200K asymptomatic carriers for a longitudinal neuroimaging study, and described clinical and radiological data of pheno-convertors. Their results show that MRI imaging by itself may not be sufficiently sensitive to detect changes during the pre-symptomatic stage [18]. In the attempt to find surrogate markers in the serum and CSF of patients with CJD or those that are at risk of developing the disease, Steinacker et al. reported increased neurofilaments (NF’s) and Tau protein in the serum of patients with CJD. In one asymptomatic carrier of prion disease, NF’s in CSF were elevated before symptoms’ onset [19], raising the question of their role as early biomarkers that may predict disease onset.

It has become increasingly evident that sleep dysfunction commonly accompanies chronic neurodegenerative conditions and may predate the onset of overt symptoms of these disorders by several years [20–23]. For example, rapid eye movement (REM) sleep behavior disorder (RBD) may precede the development of a synucleinopathy by decades [24–27], and reduced sleep efficiency is seen in patients with preclinical AD [28]. Sleep disturbances have not been included as a principal symptom of CJD [29]. However, prior studies on sleep characteristics in CJD demonstrate that sleep disturbances are common in patients with CJD [30–32], with one study showing nearly 90% of patients with at least one sleep-related complaint at the time of their initial evaluation. The most frequently observed polysomnography (PSG) aberrations were loss of normal sleep EEG architecture and the presence of sleep-disordered breathing. 38% of patients who achieved REM sleep on PSG met the criteria for REM sleep without atonia (RSWA) [31]. In a recent case report, a 60-year-old man presented with a 5-year history of REM behavior disorder, followed by rapid-onset constitutional symptoms and neurological decline, and was ultimately diagnosed with CJD. This case sheds light on the potential early REM sleep disturbances in CJD [33]. While RBD has not been established as a primary symptom of CJD, evidence of this disorder preceding the diagnosis of CJD or accompanying the disease progression has been reported in the literature [30].

Currently, there are no disease-modifying treatments available for CJD, although there are several treatments at different phases of pre-clinical and clinical trials. Identifying early subtle signs of CJD in individuals at risk of developing the disease due to their genetic status by combining multiple biomarkers (fluid biomarkers, advanced imaging, and electrophysiological biomarkers) will allow for better risk stratification of conversion into disease. This in turn will enable intervention in the future, at the prodromal stage, before symptoms’ onset. A better understanding of the trajectory of the disease will enable us to identify the window of opportunity for treatment before significant neurodegeneration has taken place. Risk stratification for mutation carriers will also allow a personalized-based approach regarding inclusion in interventional clinical trials, the timing of medical treatment (when it becomes available), and better consultation regarding lifestyle modifications and prognosis. Establishing a well-defined, large, genetically homogeneous cohort of healthy carriers of the E200K mutation (at-risk population for gCJD) in a longitudinal design with repeated collections of multiple biomarkers will enable this risk stratification, and assessment of the safety and efficacy of future treatments.

We established a longitudinal natural history study of first-degree relatives of gCJD with the following aims: To identify biological markers of preclinical CJD and to identify risk factors for phenoconversion. To achieve these aims we collect extensive longitudinal clinical, imaging, and neurophysiological data as well as body fluid and tissue-based biomarkers from healthy and at-risk individuals.

## Design and methods

### Study aims

To identify biological markers of preclinical CJD and risk factors for phenoconversion.

### Study design

The study has two main groups: A group of patients diagnosed with CJD, who are carriers of E200K mutation in the *PRNP* gene (gCJD), and a group of first-degree healthy relatives (HR) (both carriers and non-carriers of the E200K mutation in the *PRNP* gene) of patients diagnosed with gCJD.

At baseline, and at the end of every year, participants are invited for an “in-depth” visit, which includes a clinical evaluation, blood and urine collection, gait assessment, brain MRI, lumbar puncture (LP), and PSG. At 6 months from baseline, and then halfway through each year, participants are invited for a “brief” visit, which includes a clinical evaluation, short cognitive assessment, and blood and urine collection (Fig. 1). Participants diagnosed with gCJD will be invited for an extensive visit that encompasses a clinical evaluation, blood and urine collection, gait analysis, brain MRI, LP, and PSG. Given the progressive nature of the disease, patients will only undergo the assessments they can complete. The comprehensive schedule of activities for HR and gCJD patients has been detailed in the supplementary material (Table S1, S2) .

**Fig. 1 Fig1:**
[figure not shown]
Study design

After obtaining informed consent, participants undergo a physical and neurological evaluation performed by a certified neurologist. The participant’s medical and family history will be reviewed as well as his or her concomitant medications. An experienced clinical researcher will then perform the cognitive and gait evaluations and will help participants fill in several questionnaires. The participant is fitted with a gait home-monitoring device and will have direct contact with the study personnel. HR will be encouraged to contact the investigators if any symptoms or medical issues emerge between visits. All Participants will then be scheduled for LP, MRI, and PSG tests. These procedures will be performed on different days but all within 90 days (preferably within 30 days) from the clinical assessment and the provision of the biological samples.

### Study population

Inclusion/ exclusion criteria.

gCJD patients’ inclusion criteria:

Diagnosis of CJD at baseline/ screening.Age 18 years or older at baseline.Confirmation of E200K mutation or willingness to undergo genetic testing as part of the pre-screening for new patients.Ability to provide written informed consent under Good Clinical Practice (GCP), International Conference on Harmonization (ICH), and local regulations, or having a person with a power of attorney willing to provide written informed consent.

gCJD patients’ exclusion criteria:

Any other medical or psychiatric condition or laboratory abnormality, which in the investigator’s opinion might preclude participation.Previously obtained MRI scan with evidence of clinically significant neurological disorder other than CJD.Current anticoagulant treatment (e.g. Non-vitamin K Antagonist Oral Anticoagulants (NOACs), Warfarin, Low Molecular weight Heparin) that might preclude safe completion of LP.Conditions that preclude the safe performance of LP, such as severe lumbar spinal disease, bleeding diathesis, or clinically significant coagulopathy or thrombocytopenia.Conditions that preclude the safe performance of MRI scannings such as subjects who have a pacemaker, aneurysm clips, artificial heart valves, ear implants, metal fragments or foreign objects in the eyes, skin, or body, or any other known contra-indication for MRI.Active malignant disease.

Healthy relatives (HR) inclusion criteria:

First–degree relative of an E200K gCJD patient.Age 50 years or older at baseline.Willingness to undergo genetic testing.Ability to provide written informed consent under GCP, ICH, and local regulations.Willingness and ability to comply with scheduled visits, required study procedures, and laboratory tests.

Healthy relatives’ exclusion criteria include a clinical diagnosis of CJD. Otherwise, exclusion criteria are the same as those described for gCJD patients.

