### Sample size calculation and statistical analysis

With the objective of identifying biological markers for early detection of gCJD, we intend to conduct a comparative analysis of marker levels between gCJD patients and healthy individuals, as well as between healthy carriers and non-carriers. Based on the Israel National Registry for CJD, the annual incidence rate of CJD is 51 cases, although this is believed to be an underestimation. About two-thirds of the reported cases are familial cases, and of these cases, almost all are carriers of the E200K mutation. Given our conservative estimate that 50% of new cases of gCJD will be referred to our center, we anticipate that we will receive 15 new gCJD patients each year, for a total of 60 patients during the study period. Furthermore, we anticipate that approximately one-third of these patients, or 20 in total, will be willing to participate in the study.

With a conservative estimation of 3 first-degree HR per gCJD patient, this enables a population pool of > 100 per study period. As the E200K is an autosomal dominant mutation, 50% of the first-degree relatives of gCJD will carry the mutation. Based on Spudich et al. [34], the likelihood of developing gCJD is 0.45 in the age group of 51–60. According to Minikel et al., the average annual probability of onset (phenoconversion) for healthy carriers aged 40 to 80 years is 4.6% [35]. The primary aim of the study relates to biological markers for identifying phenoconversion. In our study, we referred to a positive CSF RT-QuIC.

CSF RT-QuIC has proven to be a relatively sensitive (73-97%) [13, 14] and a highly specific biomarker (99-100%) [12, 15–17] for diagnosing CJD, and it is now part of the standard diagnostic criteria [10]. Thus, considering a conservative estimate of a 13.6% phenoconversion rate among carriers (calculated as 3.4% expected conversion per year for 4 years) a sample size of 106 healthy relatives (53 carriers and 53 non-carriers) is required, based on a desired probability of type 1 error of 0.05 and a power of 80% (https://clincalc.com/stats/samplesize.aspx).

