Secondary outcomes relating to the risk of phenoconversion will be also examined. With the objective of identifying risk factors for phenoconversion, we intend to conduct a comparison between groups (gCJD patients vs. HR), and within the HR group (carriers vs. non-carriers). We also intend to perform a Cox proportional hazards analysis. The analysis is based on the concept of hazard, which is a measure of the instantaneous risk of the event occurring at a given time. The Cox model assumes that the hazard for each individual is proportional to the hazard for others over time, and can be represented as a combination of individual-specific factors and their coefficients. The coefficients from the Cox model can be used to estimate the relative risk of phenoconversion for each factor, with larger coefficients indicating a greater risk of disease onset. By examining the relationship between the risk factors and phenoconversion time, Cox proportional hazards analysis can help identify which factors are most important in determining the risk of disease onset, allowing for the development of predictive models and the identification of potential targets for intervention.

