Data Quality Control: To ensure data quality, a trained research assistant will perform regular data entry checks, and all data will be reviewed by the principal investigator to identify and resolve any discrepancies. Data monitoring: The local and the Ministry Of Health (MOH) IRB’s are responsible for conducting periodic audits on the conduct of the trial. The study meets all of the ethical and regulatory requirements for data collection and use and does not require additional oversight. Data Backup: Daily backups of all study data will be stored off-site, in a secure location, to ensure data integrity and protect against loss or corruption. Data Access: Only authorized personnel, who have completed confidentiality agreements, will have access to the study data. All study personnel will be trained on data security protocols. Data Analysis: Statistical analysis of the data will be performed using appropriate software. Data will be examined for normalcy and homogeneity based on scatter plots and histograms. Differences between groups on clinical and biological measures will be performed using General Linear Models for repeated measures. Estimation of risk based on aggregated measures will be done using cox regression. Data Sharing: The study data will be shared with relevant researchers and institutions in accordance with the study’s approved data-sharing plan. All data sharing will be done in a secure and confidential manner, and in compliance with relevant privacy regulations. Communication of trial results will be done via publication in scientific journals and professional conventions, or other data-sharing arrangements. Data Archiving: All study data will be archived and stored in a secure location for a minimum of 10 years after the completion of the study. Trial registration: The study is an observational study. It has registered retrospectively in https://clinicaltrials.gov/ and has been assigned an identification number NCT05746715.

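### Entry ages (patients from 18, relatives from 50) and the loss of converting carriers make an age imbalance likely in both marker contrasts, and the article names nothing to offset it

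*Protocol article*

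**What the plan says.** Under Study population, patients with gCJD are eligible at "Age 18 years or older at baseline" and healthy relatives at "Age 50 years or older at baseline". Neither group has an upper age limit. A clinical diagnosis of CJD excludes a relative.

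Under Sample size calculation and statistical analysis, the stated intention is that "we intend to conduct a comparative analysis of marker levels between gCJD patients and healthy individuals, as well as between healthy carriers and non-carriers". The same two contrasts are used again for risk factors. For those, a Cox model is also planned, in which the hazard "can be represented as a combination of individual-specific factors and their coefficients"; the factors are not listed.

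Under Data management, the model for marker differences is given in one sentence: "Differences between groups on clinical and biological measures will be performed using General Linear Models for repeated measures". No covariate is named.

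On onset, the Background says that "the penetrance of the mutation approaches 100" per cent and that carriers "most remain asymptomatic until middle age, and some develop the disease as late as 80 years old". The sample size section adds that "the average annual probability of onset (phenoconversion) for healthy carriers aged 40 to 80 years is 4.6" per cent.

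**The concern.** Two features fixed by the design can make the compared groups differ in age.

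- **Patients v relatives.** The age floors differ by 32 years. A patient aged 18 to 49 has no comparator of that age, and recruiting more relatives does not change this.
- **Carriers v non-carriers.** A carrier who converts can no longer be enrolled as a healthy relative, while a non-carrier of the same age can. Healthy carriers therefore become scarcer with age, and those who remain are younger on average.

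Gait, cognition, sleep and structural MRI measures may all change with age. In the carrier contrast the direction is unhelpful: younger carriers would look better on measures that worsen with age, which could hide the subtle early signs that the study is looking for.

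**Working it through.** **1. The plan's own figure.** The 106 comes from comparing a 13.6% conversion rate in carriers with an implied 0% in non-carriers, two-sided 5%, 80% power, pooled variance, no continuity correction. The mean proportion is 0.136/2 = 0.068.

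n = [1.96·√(2·0.068·0.932) + 0.842·√(0.136·0.864)]² / 0.136² = 52.6, so 53 per group and 106 in total.

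The stated figure is reproduced. It compares two proportions and contains no age term, so the point below does not alter it.

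**2. Depletion of healthy carriers.** Inputs from the sample size section: 50% of first-degree relatives carry the mutation; onset is 4.6% a year (quoted) or 3.4% a year (the plan's conservative rate). Assumption: the rate r is constant from age 40. The share of carriers still healthy at age a is S(a) = (1 − r)^(a − 40), and carriers make up S/(1 + S) of healthy relatives.

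| Age | S at 3.4% | Carrier share | S at 4.6% | Carrier share |
|---|---|---|---|---|
| 50 | 0.708 | 41% | 0.624 | 38% |
| 60 | 0.501 | 33% | 0.390 | 28% |
| 70 | 0.354 | 26% | 0.243 | 20% |
| 80 | 0.251 | 20% | 0.152 | 13% |

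**3. Resulting age gap.** Assumption: non-carriers are uniform from 50 to an upper age U. Carrier ages are the same distribution weighted by exp(−h(a − 40)), with h = −ln(1 − r), which is 0.0346 or 0.0471. The standardised gap d is the difference in means divided by the root mean square of the two SDs.

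| U | Non-carrier mean | Carrier mean, 3.4% | Gap (d) | Carrier mean, 4.6% | Gap (d) |
|---|---|---|---|---|---|
| 70 | 60.0 | 58.9 | 1.1 y (0.20) | 58.5 | 1.5 y (0.27) |
| 75 | 62.5 | 60.7 | 1.8 y (0.25) | 60.1 | 2.4 y (0.34) |
| 80 | 65.0 | 62.5 | 2.6 y (0.30) | 61.6 | 3.4 y (0.40) |

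**4. Effect on a test that leaves age out.** Let ρ be the marker–age correlation (assumed 0.3 to 0.6). The spurious standardised difference is ρ·d. With 53 per group its standard error is √(2/53) = 0.194, and the rejection rate under no true difference is Φ(−1.96 + ρd/0.194) + Φ(−1.96 − ρd/0.194).

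- Smallest case: ρ = 0.3, d = 0.20, ρd = 0.06, rejection about 6%.
- Largest case: ρ = 0.6, d = 0.40, ρd = 0.24, rejection about 24%.
- A simpler scale: if a marker changes by 0.03 SD a year (assumed), the 4.6% gaps of 1.5 to 3.4 years give 0.05 to 0.10 SD, and rejection of about 6% to 8%.

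**5. Patients v relatives.** No group gap can be computed, because the article gives no patient ages. Under the same constant rate and a flat population, the share of onsets from 40 to 80 that fall before 50 is (1 − S(50))/(1 − S(80)): 0.292/0.749 = 39% at 3.4%, and 0.376/0.848 = 44% at 4.6%. If the population also thins by 3% a year with age, the shares are 51% and 56%. These are probably upper values, because a constant rate from 40 is likely to overstate early onset. They show only that patients under 50 are plausible among the 20 or so expected.

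**The case against.** The tempting stronger reading is that both contrasts are unadjusted and therefore confounded by age. The documents do not support it. General Linear Models and Cox models can both carry age, and a condensed article may leave its covariate list to a full protocol or analysis plan that is not shown. Nor is an age floor an age distribution: if most carriers fall ill from middle age onwards, the floor of 18 for patients may be largely nominal. Both objections stand, so the point is a likely imbalance with no stated remedy, not a demonstrated bias.

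Four further objections carry weight.

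- **Size.** A shift of 0.05 to 0.10 SD is small beside the 0.54 SD detectable with 80% power at 53 per group (2.80 × 0.194). The 24% needs a correlation of 0.6 and the widest age range.
- **Direction for patients.** If patients were younger, age would make them look better on measures that worsen with age, which is conservative for finding disease effects. This is fair, but patient ages are unknown, so the direction cannot be relied on.
- **Repeated measures.** A constant age offset cancels in within-person change. This helps the carrier contrast where change over time is compared. It does not help comparisons of level, and patients have only one in-depth visit, so their contrast remains cross-sectional.
- **Primary marker.** The sample size rests on RT-QuIC positivity, and nothing suggests that age confounds that comparison. This is accepted in full.

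What survives is narrower than a missing covariate list. The unequal age floors and the loss of converters are features of the stated design, and nothing in the article recognises or offsets them.

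**Conclusion.** The point holds in a limited form. The eligibility rules and the article's own onset rates make an age imbalance likely in both marker contrasts, and no matching or age adjustment is named. For carriers v non-carriers the expected gap is about 1 to 3.5 years, given uniform ages from 50 and a constant 3.4% or 4.6% a year from age 40; the 4.6% is quoted only as an average over 40 to 80. The resulting bias is modest and matters mainly for continuous markers that are strongly related to age. For patients v relatives the gap cannot be sized from the documents, but any patient under 50 lies outside the relatives' age range. The 106 is unaffected.

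**What to change.** In the sample size and statistical analysis section, and in the data analysis text under Data management, state that baseline age is a covariate in the General Linear Models for both contrasts. With about 20 patients, a linear age term is enough in the patient v relative model.

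Add a repeat of the patient v relative contrast restricted to patients aged 50 or older. Below 50 there are no relatives, so an age term there only extrapolates; the restricted analysis shows whether the result depends on that.

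Sex may be added but is optional, since the argument here concerns age. The cost is a sentence or two: age is known from eligibility and demographics are collected on all participants. Eligibility, visits and sample size do not change.
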